### Statistical analysis

Simple summary statistics will be calculated to describe demographic, procedure, process and outcome data. Categorical data will be summarised by counts and percentages and continuous data by median, IQR and range.

We will establish the proportion and 95% CIs of patients experiencing implant loss and other key safety outcomes (readmission for complications, reoperation and infection) at 3 months and compare these with findings with those reported in the iBRA study.^7^

An exploratory risk factor analysis will be conducted to explore the impact of type of mesh and known risk factors for complications including smoking; BMI and radiotherapy if sufficient numbers of patients are recruited to the study.

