#### Exclusion criteria

Absolute and relative exclusion criteria will be used to reflect current practice and account for the variable experience of surgeons performing PPBR across the UK. Absolute exclusion criteria will be applied to all patients. Relative exclusion criteria can be applied flexibly according to the surgeon’s experience with the procedure in conjunction with the patient’s consent following discussion that the risk of complications may be increased in this setting.

Absolute exclusion criteria

Patients assessed as having insufficient soft tissue coverage for PPBR by the operating surgeon.Patients having revisional or delayed breast reconstruction.Patients unable or unwilling to provide informed consent.

Relative exclusion criteria reflect ABS/BAPRAS guidelines for mesh-assisted breast reconstruction^32^ and include the following:

Current smokers or recent ex-smokers (<6 weeks).Previous breast/chest wall radiotherapy.Body mass index (BMI) of greater than 30.Reconstruction with an implant of more than 600cc.Patients anticipated to require postmastectomy radiotherapy.Poorly controlled diabetes.

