#### Standardisation of surgical technique and procedure fidelity

All patients will undergo a skin or nipple-preserving mastectomy followed by an immediate IBBR.

Participating surgeons will undertake the procedure as per their standard practice. Mesh choice (biological or synthetic and the product used) and implant selection (fixed-volume; adjustable implants or tissue expanders) will be as per surgeon preference. All patients will be planned for a prepectoral reconstruction prior to surgery.

The following steps of the PPBR procedure will be considered mandatory, prohibited and discretionary according to the typology described by Blencowe *et al.*
33

*Mandatory*—insertion of a tissue expander/adjustable implant or fixed-volume implant.
*Prohibited*—raising the pectoralis muscle.
*Discretionary*—all other steps of the procedure.

If the surgeon considers that prepectoral reconstruction is not possible at the time of surgery or modifies the planned procedure (eg, inserts tissue expander rather than fixed-volume implant), this will be recorded on the case report form (CRF) with reasons for the modification (eg, thin skin-flaps). Details of the alternative procedure performed (eg, subpectoral reconstruction) will be collected. Surgeons will also be encouraged to record any learning arising from the case.

Strategies to minimise infection (eg, use of laminar flow, cavity irrigation, and glove change) will be as per local practice but participating centres will be encouraged to adhere to published best practice guidelines^32 34^ and use the evidence-based Manchester checklist.^35^

Use of drains and other concomitant interventions (eg, antibiotics, dressings) will be permitted as per local practice.

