### Data analysis and sample size

#### Prepectoral safety and effectiveness

##### Sample size

A single-arm two-stage design will be used to assess the safety of PPBR based on the primary outcome of implant loss rate at 3 months. It is expected that the implant loss rate will be 9% or lower based on findings from the recent iBRA study;^7^ 15% or greater will be deemed unacceptably high.

A sample size of 310 patients would result in a two-sided 95.0% CI for a single proportion, assumed to be 0.10, with a width equal to 0.070. Allowing for a 10% loss to follow-up at 3 months at least 341 patients will be recruited to inform a future trial with implant loss as the primary outcome.

Based on data from the iBRA study, the number of prepectoral reconstructions performed at each site is likely to be small (4–40 per year).^7^ We will therefore aim to recruit from between 20 and 30 sites over a period of 12 months.

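### The planned 95% CI width of 0.070 assumes independent patients and makes no allowance for clustering by site or surgeon, so the stated precision is optimistic under any positive intracluster correlation

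*Protocol article*

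**What the plan says.** The Sample size section of the protocol article bases the study on precision: 310 evaluable patients give a "two-sided 95.0% CI for a single proportion, assumed to be 0.10, with a width equal to 0.070". The same section expects a loss rate of 9% or lower, calls 15% or more unacceptable, puts site volume at 4–40 cases a year, and plans 20–30 sites. The Abstract gives 30–40 centres.

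The Statistical analysis section then states: "We will establish the proportion and 95% CIs of patients experiencing implant loss and other key safety outcomes". It names neither an interval method nor a clustering term. It adds an exploratory analysis, if enough patients are recruited, to "explore the impact of type of mesh and known risk factors for complications including smoking; BMI and radiotherapy".

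Other sections describe variation between surgeons and sites:
- Standardisation of surgical technique and procedure fidelity: the choice of mesh and implant "will be as per surgeon preference", infection control follows local practice, and all steps are discretionary apart from one that is mandatory and one that is prohibited.
- Exclusion criteria: surgeon experience is acknowledged to vary, and "Relative exclusion criteria can be applied flexibly" in line with it.
- Introduction: reducing learning-curve effects is part of the rationale for the mixed-methods design.

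**The concern.** If the risk of implant loss differs between surgeons or sites, patients treated by the same team have correlated outcomes. The pooled proportion then varies more than a binomial count of 310 independent patients. A width planned on independence is too small, and an interval computed the same way would cover the true rate less often than its nominal level.

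The protocol gives its own reasons to expect such variation, so the independence behind the 0.070 needs either a justification or an allowance. What is at stake is how firmly the study can say that loss lies below the 15% it calls unacceptable. Under Design of the main study, a future randomised trial depends on the technique being considered safe.

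There is a smaller, related point. Because the surgeon chooses the mesh, a comparison of mesh types is in large part a comparison of surgeons or sites.

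**Working it through.** **Inputs from the protocol article.** Sample size section: n = 310, p = 0.10, two-sided 95%, width 0.070, 20–30 sites. Abstract: 30–40 centres.

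**Assumed inputs, not in the documents.** ICC 0.01 to 0.05, and coefficient of variation (CV) of site size 0 or 0.6. Site stands in for the cluster because the number of surgeons is not given.

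**Step 1: reproduce the plan's figure.** Width at 31/310 with independent patients:
- Exact (Clopper-Pearson): 0.0690 to 0.1389, width 0.06997. By this method 310 is the smallest n with width at most 0.070.
- Wald: 2 × 1.96 × √(0.10 × 0.90 / 310) = 0.0668.
- Wald with continuity correction: 0.0668 + 1/310 = 0.0700 (strictly, n = 311 is needed).
- Wilson: 0.0671.

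The stated 0.070 matches the exact interval, and every candidate treats patients as independent. No room is left for a design effect.

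**Step 2: add clustering.** With m = 310 / number of sites, the design effect is DE = 1 + ((1 + CV²)m − 1) × ICC and the effective sample size is 310 / DE. The exact interval at p = 0.10 is then taken at that effective size. For example, with 20 sites, CV 0.6 and ICC 0.05: m = 15.5, DE = 1 + (1.36 × 15.5 − 1) × 0.05 = 2.004, effective n = 155, interval 0.058 to 0.158, width 0.101.

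Each cell gives the width, with the upper limit in brackets; the first value is for CV 0 and the second for CV 0.6.

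| Sites | ICC 0.01 | ICC 0.02 | ICC 0.05 |
|---|---|---|---|
| 20 | 0.075 (14.2%); 0.077 (14.3%) | 0.080 (14.5%); 0.084 (14.7%) | 0.093 (15.3%); 0.101 (15.8%) |
| 30 | 0.073 (14.1%); 0.075 (14.2%) | 0.077 (14.3%); 0.079 (14.5%) | 0.086 (14.9%); 0.091 (15.2%) |
| 40 | 0.072 (14.0%); 0.073 (14.1%) | 0.075 (14.2%); 0.077 (14.3%) | 0.082 (14.6%); 0.086 (14.9%) |

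The independent-patient upper limit is 13.9%. At an intermediate ICC of 0.03, only the most clustered case (20 sites, CV 0.6) passes 15%, at 15.1%.

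**Step 3: the expected rate.** At an observed 9%, the independent-patient upper limit is 12.8%. In the worst case above (20 sites, CV 0.6, ICC 0.05) it is 14.7%, still below 15%.

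**Step 4: coverage of the unadjusted exact interval.** Beta-binomial simulation with true rate 10%, CV 0.6 and 8,000 runs per setting; ranges run over 20 to 40 sites.
- Independent patients (calculated directly): 96.3%
- ICC 0.01: 94–96%
- ICC 0.02: 92–94%
- ICC 0.05: 86–91%

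**Step 5: what holding the width would need.** Multiplying 310 by DE gives roughly 331–372 evaluable patients at ICC 0.01, 352–434 at 0.02 and 415–621 at 0.05.

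**The case against.** The strongest reply is that only the planning calculation shows independence. The Statistical analysis section promises proportions with intervals and leaves the method open, and an analysis plan that is not shown may fix a clustered method. That stands. A reader might infer that the reported interval will ignore clustering and will be too narrow, but the document does not say so. The firm ground is the Sample size section.

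Second, the size of the effect rests on an ICC that nobody has supplied. At 0.01 coverage is close to nominal and the width hardly changes. That also stands, so the result has to be given as a range.

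Third, no stated rule uses the upper confidence limit. The 15% stopping criterion under Planned interim analysis applies to the observed rate, and the final intervals are to be set beside the published comparison study. So it cannot be said that clustering would overturn a decision. It bears on how convincing the evidence of safety will be.

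Fourth, a reader might infer that the risk-factor analysis is confounded by surgeon, or that effects of smoking, BMI and radiotherapy will be biased because higher-risk patients go to more experienced surgeons. The text supports only a risk for mesh. The analysis is exploratory and conditional, its factor list is open, and no model is given that leaves out surgeon. The Exclusion criteria section permits selection by experience but does not show that it happens, and any figure for the resulting bias would need invented inputs.

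Nor is a full model the obvious remedy. About 31 events (10% of 310) over 20–40 sites is 31/40 to 31/20, or about 0.8 to 1.6 events per site. Surgeons are only asked to complete the experience questionnaire, so experience may be missing for some.

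**Conclusion.** The concern holds as a point about planned precision. The 0.070 is an independent-patient width in a protocol that describes marked variation between surgeons and sites, so it is optimistic under any positive ICC. On the assumed ranges the width is about 0.072 to 0.101, and the upper limit at an observed 10% is about 14.0% to 15.8% instead of 13.9%. The effect is minor at ICC 0.01 and material near 0.05. The upper limit reaches 15% only towards the top of the ICC range with about 30 or fewer sites, and not at the expected 9%. The conflicting site counts matter because the number of sites drives the design effect.

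For the exploratory analysis, the supported conclusion is limited to this: surgeon-chosen mesh puts the mesh comparison at risk of confounding by surgeon or site.

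**What to change.** - Keep the sample size. Reconcile 20–30 sites (Sample size section) with 30–40 centres (Abstract), then restate the expected width as a range over assumed ICCs, in place of the single 0.070.
- State that the intervals for implant loss and the other key safety outcomes will take site, or surgeon where identified, as the cluster. A beta-binomial model or a GEE on the logit scale with a small-sample correction would serve.
- Say that mesh is chosen by the surgeon, that its comparison will be interpreted as open to confounding by surgeon or site, and that clustering will be allowed for in the exploratory analysis where event numbers permit.

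This changes wording and analysis only and needs no extra patients. The cost is a somewhat wider stated interval, and the cluster-adjusted method will itself be imprecise with about 31 events.

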#### Specific objectives

To establish the short-term safety (implant loss; infection; reoperation and readmission at 3 months) and effectiveness (patient-reported outcomes using BREAST-Q at 3 and 18 months) of PPBR compared with published national standards from the National Mastectomy and Breast Reconstruction Audit^31^ and iBRA^7^ studies.To explore the feasibility of using a novel mixed-methods approach in an IDEAL 2a/2b study to promote shared learning and identify intervention stability including the acceptability of the methodology to surgeons and the most effective methods for providing feedback.To inform the feasibility, design and conduct of a future RCT including the numbers of patients at participating centres undergoing IBBR who are eligible for PPBR; types of meshes used and approach to concomitant interventions.To build capacity to deliver a future RCT by establishing a network of surgeons engaged in the need for evaluation who are able to perform PPBR to a high standard and who will participate in a future study.

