## Outcome measures

### Safety and effectiveness outcomes

The primary outcome for the prepectoral safety study will be implant loss at 3 months defined as the removal of the implant or tissue-expander without replacement as a result of a complication. This is consistent with the definition used in the iBRA study.^7^ Secondary safety and effectiveness outcomes:

Postoperative pain assessed by patient self-report using a visual analogue scale at 24 hours, 1 week, 2 weeks and 3 months.Complications requiring readmission and/or reoperation at 3 months.Infection defined as (i) minor—requiring treatment with oral antibiotics, (ii) major requiring admission for intravenous antibiotics and/or surgical debridement.Quality of life including satisfaction with breasts; physical well-being; psychosocial well-being and animation assessed using the validated BREAST-Q^36^ questionnaire at 3 and 18 months following surgery.Further surgery for complications or cosmesis at 18 months

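### The planned comparison of implant loss with the published iBRA rate states no case-mix adjustment, so it is open to selection bias, plausibly but not provably in favour of prepectoral reconstruction

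*Protocol article*

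**What the plan says.** All places are in the protocol article.

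- **Specific objectives.** The first objective is to establish the short-term safety and effectiveness "of PPBR compared with published national standards from the National Mastectomy and Breast Reconstruction Audit" and from iBRA.
- **Safety and effectiveness outcomes.** The primary outcome is implant loss at 3 months. On its definition the article says: "This is consistent with the definition used in the iBRA study".
- **Statistical analysis.** Implant loss, readmission, reoperation and infection are given as proportions with 95% CIs, and the analysts will "compare these with findings with those reported in the iBRA study". No standardisation, matched subset or margin is stated. A separate exploratory analysis of mesh type, smoking, BMI and radiotherapy follows if numbers allow. These last three are described there as known risk factors for complications.
- **Sample size.** The benchmark is: "It is expected that the implant loss rate will be 9% or lower based on findings from the recent iBRA study". The upper limit is: "15% or greater will be deemed unacceptably high".
- **Inclusion and Exclusion criteria.** The surgeon must judge the woman technically suitable for PPBR. One absolute exclusion is: "Patients assessed as having insufficient soft tissue coverage for PPBR by the operating surgeon". Smoking, previous or anticipated radiotherapy, BMI over 30, implants over 600cc and poorly controlled diabetes are relative criteria, and "Relative exclusion criteria can be applied flexibly".
- **Participant screening.** The log covers all women electing immediate implant-based reconstruction under participating surgeons. It records why some are not suitable for PPBR, with smoking and previous radiotherapy as example reasons.

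**The concern.** A single-arm study that reads its safety result against an outside series needs the two groups to carry similar baseline risk, or needs an allowance for the difference. Here the outcome definition is aligned with iBRA, but the case mix is not addressed. The eligibility rules can act on the same variables that the article names as risk factors. The screening log shows that the authors expect some women already electing implant-based reconstruction to be kept out of PPBR for those reasons. If the Pre-BRA cohort is lower risk than iBRA as a result, a loss rate equal to iBRA's would mean that PPBR performs worse in like patients.

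The section on the design of the main study makes the step to a randomised trial depend on PPBR being considered safe. The summary of strengths and limitations offers the iBRA comparison as the answer to having no internal control group. A reassuring match with iBRA will therefore carry weight, and its meaning depends on who was selected.

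**Working it through.** **1. The plan's own precision figure.** The article states: "A sample size of 310 patients would result in a two-sided 95.0% CI for a single proportion, assumed to be 0.10", with a width of 0.070. At n = 310 and p = 0.10 the exact (Clopper-Pearson) interval has width 0.0700, so the figure is reproduced. (The plain Wald width is 0.0668.)

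**2. What a result at the benchmark would look like.** 28 losses in 310 is 9.0%, with an exact 95% CI of 6.1% to 12.8%.

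**3. Case-mix model.** Inputs:

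- Benchmark rate 0.09, from the Sample size section.
- f = share of iBRA patients with a risk factor, g = the same share in Pre-BRA, RR = relative risk of implant loss with the factor. The documents give none of these three. All values below are assumptions.

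Formulas:

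- Low-risk rate: r = 0.09 / [(1 − f) + f·RR]
- Rate expected in Pre-BRA if PPBR is exactly as safe as the benchmark: E = r·[(1 − g) + g·RR]
- True risk ratio concealed by an observed 9%: 0.09 / E

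Example: f = 0.4, g = 0.1, RR = 3 gives r = 0.09/1.8 = 0.050, E = 0.050 × 1.2 = 0.060 and a ratio of 0.09/0.060 = 1.50.

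| f | g | RR | r | E | Concealed ratio |
|---|---|---|---|---|---|
| 0.3 | 0.1 | 2 | 6.9% | 7.6% | 1.18 |
| 0.3 | 0.2 | 2 | 6.9% | 8.3% | 1.08 |
| 0.3 | 0.1 | 3 | 5.6% | 6.75% | 1.33 |
| 0.3 | 0.2 | 3 | 5.6% | 7.9% | 1.14 |
| 0.4 | 0.1 | 2 | 6.4% | 7.1% | 1.27 |
| 0.4 | 0.2 | 2 | 6.4% | 7.7% | 1.17 |
| 0.4 | 0.1 | 3 | 5.0% | 6.0% | 1.50 |
| 0.4 | 0.2 | 3 | 5.0% | 7.0% | 1.29 |

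Every row assumes g < f, so every row favours PPBR by construction. Two other cases belong beside them:

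- Equal shares (g = f): E = 9.0%, ratio 1.00, no bias.
- Higher share in Pre-BRA, for example f = 0.2, g = 0.3, RR = 2: r = 0.09/1.2 = 7.5%, E = 7.5% × 1.3 = 9.75%, ratio 0.09/0.0975 = 0.92. The bias now runs against PPBR.

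**4. Would the planned interval reveal it?** Seven of the eight expected rates in the table lie inside the 6.1–12.8% interval from step 2, and the eighth (6.0%) lies just below it. A shift of this size would not show in the crude comparison.

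**5. A shortcut that makes things worse.** With only an overall iBRA rate, one might compare Pre-BRA patients without risk factors with that overall 9%. At equal safety those patients would show r, which is 5.0% to 6.9% in the table. The concealed ratio becomes 0.09/0.0692 = 1.30 to 0.09/0.050 = 1.80, larger than the 1.08 to 1.50 from the full cohort.

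**The case against.** The other side has several good arguments.

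- **Selection is soft.** Only insufficient soft tissue is absolute among the risk-related criteria. The others are flexible, and recruitment is of consecutive suitable women. This stands: the documents permit selection on the risk factors but do not impose it.
- **iBRA may have been selected in the same way.** The relative criteria come from general guidance for mesh-assisted reconstruction, and iBRA's eligibility and case mix are not in the documents. This stands against any firm claim on direction or size. The screening log still anticipates a filter between implant-based reconstruction in general and PPBR, which is why a lower-risk cohort is plausible.
- **Other forces push the other way.** The article discusses learning-curve effects and allows for surgeons new to the technique, which could raise the observed rate. This also stands.
- **The fixed decision limit is absolute.** The study stops at 15% or more at the interim analysis, and no test or margin is tied to 9%. That is true, but the limit takes no account of case mix either, and a final 9% is well below it. The reading against iBRA remains the stated route to the first objective.
- **This is a disclosed single-arm feasibility cohort, and an analysis plan may add adjustment.** The lack of an internal control is acknowledged. However, the remedy offered is the outside comparison itself, and the exploratory risk-factor analysis is not described as adjusting it. An unseen plan may do more; the point concerns the comparison as the article states it.

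A reader might go further and infer that iBRA is the only comparator, or that the bias certainly favours PPBR. The documents support neither. The objectives also name the national audit, the summary of limitations mentions national quality standards, and the direction depends on a case mix that is not given.

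**Conclusion.** The point holds in a limited form. The comparison of implant loss with iBRA is stated without any case-mix adjustment, and eligibility can act on smoking, BMI and radiotherapy, which the article itself counts as risk factors. The comparison is therefore open to case-mix bias, plausibly in favour of PPBR but not demonstrably so.

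The size cannot be derived from the documents. It is nil if the two cohorts have the same risk-factor share. It is a concealed ratio of about 1.1 to 1.5 under the assumed shares of 30–40% in iBRA and 10–20% in Pre-BRA with relative risk 2–3. It is reversed if Pre-BRA has the higher share. The 1.1–1.5 range illustrates what could go unnoticed; it is not an estimate of the bias. The point is worth correcting because the result informs whether PPBR is considered safe enough for a trial, and the correction is cheap.

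**What to change.** 1. Tabulate the prevalence of smoking, BMI over 30, previous radiotherapy and the other relative criteria in Pre-BRA beside iBRA's figures.
2. Where iBRA loss rates by smoking, BMI over 30 and previous radiotherapy can be obtained, standardise indirectly. The expected number of losses is the sum over strata of the Pre-BRA stratum size times the iBRA stratum rate. Report observed/expected implant loss beside the crude rates, with an interval that includes the sampling error of both series. This needs iBRA counts cross-classified by the factors, not separate rates for each one.
3. If only aggregate iBRA figures are available, do not set a low-risk Pre-BRA subset against the overall iBRA rate (step 5 of the working). Report the crude comparison as descriptive and limit the conclusion to women selected as suitable for PPBR.

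**Cost.** A change in the analysis text and a request for iBRA stratum counts. The article calls this project an extension of iBRA, which suggests such counts might be obtainable but does not establish it. Pre-BRA already collects demographic, comorbidity and operative data. The interval will be somewhat wider. With about 28 losses expected (9% of 310 = 27.9), the strata must be few. Standardisation on these factors will not remove selection on soft tissue coverage, and the report should say so.
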